### Sample size

Previous NHS GG&C studies,^10 21^ combined with internal audit data (showing that 80% of patients have direct or daily smartphone, tablet or web access), indicate that recruitment of 400 participants across a 12-month period is feasible, and likely to provide adequate data to conduct meaningful primary and secondary endpoint analyses.

An improvement in admission-free survival, with reduction in admissions by one per patient per year is projected, if support for provision of evidence-based COPD care is achieved by the service model. As the feasibility of an end-to-end digitalised service model for COPD has not yet been tested, and the service components will be adapted during the study, sample size power calculations and randomisation are not yet appropriate.

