### Subsequent assessments

Participants will be recruited into the digitalised service model over a 12-month period. Observation of secondary endpoints will be continued over the 12-month period following recruitment. Participants who are recruited will subsequently continue within the digital service model beyond the trial period, either until ongoing procurement of the service infrastructure is established, or transition to alternative equivalent service model is completed.

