### Data from PROs

Participants (or their family or carer) will complete PRO questionnaires in the patient web portal. Daily SMS and/or email notifications are provided as a prompt to complete these. There is support information in the associated website to assist participants with any difficulties with the patient portal. Additional support will be provided by the clinical users if required.

Participants will complete symptom diary and COPD assessment tool (CAT) questionnaire daily. Medical Research Council dyspnea score (MRC) and healthcare episode questionnaires will be completed weekly. EQ-5D-5L generic quality of life questionnaire will be completed every 4 weeks. These questionnaires have been integrated to improve question flow and simplify the user experience. Questionnaire flow content is included in the online supplemental material 1.

10.1136/bmjresp-2021-000905.supp1Supplementary data

PRO data are presented unmodified, in a ‘user-friendly’ format (co-designed with clinical users), in the clinician dashboard. These unmodified data will inform and enhance clinical encounters and patient–clinician communication.

Pilot user experience research shows that the daily PRO questions can be completed in ~70 s, with weekly questions taking an additional 90 s, and monthly generic quality of life questions taking an additional 5 min.

Specific permission for use of CAT questionnaire within this e-health system has been obtained. The use of other PROs is covered by available open licensing.

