## Study outcome measures

Primary and secondary endpoints for the RECEIVER Study are shown in table 1.

**Table 1 T1:** RECEIVER primary and secondary endpoints

Primary endpoint	Proportion of enrolled high-risk participants with COPD who use remote management in a digital service model
Secondary endpoints	Clinical outcomes, comparing impact of digitally enabled remote management versus historical and contemporary SafeHaven cohorts: Clinical events: COPD exacerbation; unscheduled care contact (digital platform, COPD team visit, primary care, emergency department, hospital admission); mortality—COPD and non-COPD related. Hospital occupied bed days preceding and subsequent 12 months (adjusted time interval if survival <12 months). Treatment uptake (where indicated): smoking cessation; pulmonary rehabilitation; vaccination; supported self-management; home oxygen; home NIV. NIV group: NIV usage, symptom change, NIV therapy parameters, blood gases during routine clinical care. Supported self-management: utilisation of self-management information (page views), number of exacerbation managed at home versus in hospital, number of rescue packs used in 12 months (captured through weekly PROs), utilisation of messaging (number of message threads), sputum microbiology (where available during routine clinical care), impact of patient activation measures (where measured during routine care). Impact of demographics, physiology and patient activation measures (where measured during routine care)—deprivation category of area of residence, age and sex, number of previous admissions, smoking status, participation in pulmonary rehabilitation in previous 2 years; lung function measurements, modelled home air pollution exposure; EMG, oscillometry and home air pollution monitoring in subset of participants where this is carried out—on outcomes, clinical events and treatment uptake. Clinical service outcomes for digital service model, remote-managed home NIV and supported self-management: Remote-managed home NIV: number, nature and complexity of NIV therapy reviews and interventions to provide. Supported self-management: number, nature and complexity of reviews and interventions to provide. Digitalised service model: user and developer time/cost required for development and modification of clinical dashboard; qualitative analysis (clinical user satisfaction and reflection on efficiency or additional workload); quantitative analysis (clinical dashboard utilisation tracking). Patient portal: user and developer time/cost required for development and modification of clinical dashboard; qualitative analysis (user satisfaction) and quantitative analysis (uptake, engagement with app and wearable, successful use of digital service vs bypass to conventional healthcare contacts). Machine learning-supported exploratory analyses of associations and relative predictive importance of electronic health record, PROs, wearable physiology and NIV parameters: Associations between changes in PROs (MRC, CAT, symptom diary, and EQ-5D-5L questionnaires) with routine clinical care interventions, COPD exacerbation and other clinical events. Associations between changes in wearable monitoring parameters (activity, sleep, heart rate variability, energy expenditure, respiratory rate) with routine clinical care interventions, COPD exacerbation and other clinical events. Associations between changes in NIV-monitored parameters (usage, leak, airway pressures, respiratory rate, tidal volume, minute ventilation, inspiratory/expiratory ratio and detected respiratory events) with routine clinical care treatment interventions, COPD exacerbation and other clinical events. Associations between changes in clinical endpoints and relative importance plots of all remote management-acquired data (including EMG, oscillometry and home pollution monitoring exploratory endpoints in subgroup these measured on) to determine contribution of these to outcome prediction, and therefore value of these for future prospective study. Patient-centred outcomes: Health-related quality of life (EQ-5D-5L) at baseline and monthly during study. Qualitative user research (planned subset of participants, convenience sample) with semistructured user experience interviews. Impact of patient activation (where this is measured at baseline and/or follow-up during routine clinical care) on enrolment and use of digital service model. Healthcare cost analyses: Development and installation costs for digitalised service model for remote management of COPD. Recurring costs (clinical staffing, digital platform hosting, digital platform scheduled update and maintenance) for digital service model for remote management of COPD. Projected direct and indirect cost-savings (admission and unscheduled care reduction, travel, carer burden impact, clinical efficiency) of high-risk COPD with digitally enabled remote management, compared with previous service model.

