## Statistics and data analysis

Secondary outcomes in the RECEIVER observational cohort will be compared with matched retrospective data from de-identified linked datasets of historical control and contemporary control high-risk patients with COPD. These will comprise of patients identified from coding and admission data as having had severe exacerbation of COPD between 1 January 2010 and 30 April 2019 (historical cohort) and between 1 July 2019 and 30 June 2020, excluding participants enrolled in the RECEIVER Study (contemporary control). The historical control dataset will contribute to machine learning models development. Secondary outcome analysis will be separately compared between the RECEIVER cohort, historical cohort and contemporary control cohort. This component of the study is also separately registered with dataset access approval from NHS GG&C SafeHaven LPAC.

The clinical endpoint data will be reported as a proportion and 95% CI for that outcome, calculated by Kaplan-Meier method. Demographic data will be presented as mean and SDs, or medians and IQRs as appropriate. Correlation, t-test, analysis of variance and effect size analyses will be used as appropriate for secondary endpoint analysis, comparing results of clinical endpoint and patient-centred outcomes with NIV therapy and supported self-management parameters.

Machine learning ensemble methods will be used to develop binary classification problems for patient risk. Precision, recall, accuracy and C-statistics of the receiver operating characteristic curve will be used to evaluate model performance.

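### Only correlation, t-test, ANOVA and effect sizes are named for relating four-weekly EQ-5D-5L to NIV and self-management parameters; a participant-level mixed model would suit these repeated, uneven series better.

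*Protocol article*

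**What the plan says.** All references are to the protocol article.

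- **Methods named.** Statistics and data analysis: "Correlation, t-test, analysis of variance and effect size analyses will be used as appropriate for secondary endpoint analysis". The sentence goes on to say what is related to what: "comparing results of clinical endpoint and patient-centred outcomes with NIV therapy and supported self-management parameters". No unit of analysis is given, and no method for several readings per person is named.
- **The outcome.** Table 1, under Study outcome measures, lists "Health-related quality of life (EQ-5D-5L) at baseline and monthly during study". Data from PROs says that the "EQ-5D-5L generic quality of life questionnaire will be completed every 4 weeks".
- **The exposure.** NIV data reach the platform through the AirView feed (Remote-monitored home NIV). Table 1 treats NIV parameters as quantities that change: "Associations between changes in NIV-monitored parameters (usage, leak, airway pressures, respiratory rate, tidal volume". Several self-management parameters in Table 1 are totals per person, such as page views, message threads and rescue packs over a year.
- **Length of follow-up.** Subsequent assessments: "Observation of secondary endpoints will be continued over the 12-month period following recruitment".
- **Uneven series.** Withdrawal of subjects lets participants cut back on questionnaires or leave, and keeps those who leave in the analyses. Table 1 allows for survival below 12 months, and Expected adverse events anticipates deaths.

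**The concern.** EQ-5D-5L and NIV use are both repeated within participants. In their ordinary form, correlation, the unpaired t-test and one-way ANOVA treat each value as independent. Applied to all readings at once, they would give intervals that are too narrow and chance associations that look real. They would also mix two questions: whether people who use NIV more differ in quality of life, and whether a person's quality of life moves with that person's own use. Only the second bears on whether the two move together during the service. The first is open to confounding, because sicker people may use NIV differently. Study limitations says that the experience gained here will form the basis for later randomised studies, so a spurious association could be carried forward.

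**Working it through.** The plan gives no power, alpha or ICC figure for these analyses, so there is no stated number to reproduce. The check asks what each way of applying the listed tests would do.

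**Inputs**
- Readings per participant: 12 months at one per 4 weeks, 52 / 4 = 13. Counting calendar months gives 12.
- Significance level: not stated; two-sided 5% is assumed, in line with the interval level in "The clinical endpoint data will be reported as a proportion and 95% CI for that outcome".
- Participants: "recruitment of 400 participants across a 12-month period is feasible"; the size of the NIV group is not given. Simulations used 50, 100 and 400 participants for the correlation, and 100 and 400 for the t-test.
- ICC: not in the document. Assumed range 0.05 to 0.7.

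**Formula for pooled readings.** With m readings per person and ICCs ρx (exposure) and ρy (outcome), the design effect is DE = 1 + (m − 1)·ρx·ρy. The true error rate of a nominal 5% test is 2·[1 − Φ(1.96/√DE)].

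**Participant-level exposure** (ρx = 1, for example total message threads or a fixed group), m = 13, so DE = 1 + 12·ρy:

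| ICC of outcome | DE | False-positive rate |
|---|---|---|
| 0.05 | 1.6 | 12% |
| 0.3 | 4.6 | 36% |
| 0.5 | 7.0 | 46% |
| 0.7 | 9.4 | 52% |

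At ICC 0.5, √7 ≈ 2.6, so pooled intervals would be about 2.6 times too narrow.

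**Exposure that also varies monthly with the same ICC**, m = 13, so DE = 1 + 12·ICC²:

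| ICC of both | DE | False-positive rate |
|---|---|---|
| 0.05 | 1.03 | 5% |
| 0.3 | 2.08 | 17% |
| 0.5 | 4.00 | 33% |
| 0.7 | 6.88 | 46% |

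With m = 12 the last three rates become 16%, 31% and 44%. If one of the two variables has no within-person correlation, DE = 1 and the rate stays at 5%.

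**Simulation under no association**
- Pooled two-group t-test, m = 13, 100 participants: 37%, 46% and 52% at ICC 0.3, 0.5 and 0.7. With 400 participants: 36%, 46% and 53%.
- Pooled correlation with both variables varying, 100 participants: 17%, 32% and 44% at ICC 0.3, 0.5 and 0.7. With 400: 18%, 34% and 46%. Sample size makes no material difference.
- Uneven series of 1 to 13 scores, participant-level exposure, pooled correlation: 10%, 29%, 37% and 44% at ICC 0.05, 0.3, 0.5 and 0.7.
- One mean per person: about 4% to 6% throughout, which is nominal.

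**What one value per person costs.** The error rate is right, but about 13 scores become one, a person with a single score counts the same as a person with thirteen, and only the between-person association remains. Unadjusted, that association carries the effect of severity.

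**The case against.** A reader might infer that the trial plans to pool all readings and will therefore report false associations several times too often. The documents do not support that. Nothing says that readings will be pooled, and the wording leaves the choice within the listed methods open. A mean or change score per person, a paired t-test and repeated-measures ANOVA all fit the listed names and can hold the 5% level. Several self-management parameters are already one total per person. Nor is one value per person the only option left within the list.

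It is also fair to say that the unit of analysis and the model terms often sit in a statistical analysis plan, that an article condenses, and that these are secondary associations in a feasibility study with no power calculation.

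What survives is narrower. The article does not leave the method open; it names a family, and that family fits these data poorly. Paired tests and classical repeated-measures ANOVA need matched or complete sets, which participants who limit questionnaires, withdraw or die will not provide. Neither relates a score to an exposure that varies over time. The machine learning analyses do use changes in PROs and in NIV parameters, but Table 1 relates each to care interventions and clinical events, not EQ-5D-5L to NIV use. Statistics and data analysis describes those models as binary classification of patient risk.

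**Conclusion.** The point holds as a cheap improvement to the named methods, not as proof that the planned analysis is invalid. The inflation is conditional on pooling and on the assumed ICCs. For a participant-level exposure it would be about 12% to 52% at ICC 0.05 to 0.7. If NIV use varies monthly with the same ICC it would be about 5% to 46%, so at the low end there is none. If each person is reduced to one value, the 5% level holds, and the cost is lost within-person information, poor weighting and confounding by severity. The firm part is that the named methods do not make good use of about 13 scores per person in series of unequal length against an exposure that changes over time.

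**What to change.** In Statistics and data analysis, for EQ-5D-5L and other repeatedly measured outcomes, name a linear mixed model (or GEE) with participant as the cluster. Include time since enrolment, baseline severity, age and sex as fixed terms. Enter NIV use as two terms, the participant's own mean and the monthly deviation from it, so that between-person and within-person associations are reported separately. Keep t-test, ANOVA and correlation for outcomes with one value per participant.

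The cost is one or two sentences and slightly more analysis code. No new data are needed: age, sex, lung function and exacerbation history are already collected under Baseline clinical data. Intervals will be wider than a pooled analysis would give, and some associations that pooling would have shown as significant will not be. Adjustment reduces confounding of the between-person term by severity but cannot be assumed to remove it.

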#### Baseline clinical data

The following data will be collated when the participant is enrolled and added to the clinical details form visible on the clinician dashboard: participant age, sex, smoking status, vaccination status, comorbidities, COPD exacerbation history, COPD medications, lung function results, key laboratory results including maximal eosinophil count and modelled home pollution exposure (QCumber platform; NO2, O3, PM2.5, black carbon).

Participants who have not had contemporary spirometry (standard lung function test) will have this repeated at the time of recruitment—this would be routine clinical care.

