### Remote-monitored home NIV

Participants with severe COPD who have standard indications (persistent hypercapnia with PCO_2_ >7 kPa and/or recurrent episodes of acute hypercapnic respiratory failure and/or COPD–obstructive sleep apnoea overlap and/or COPD with significant nocturnal hypoventilation) are commenced on home NIV in NHS GG&C using Resmed Lumis 150 ST-A device as routine clinical care. Participants with significant obstructive sleep apnoea syndrome may be alternatively commenced or transitioned to auto-titrating continuous positive airway pressure (CPAP) using an AirSense-10 device. NIV initiation and optimisation will be conducted as per standard NHS GG&C clinical protocol. NIV data capture and device adjustment will be via ResMed AirView platform, again as routine clinical care.

AirView data will be acquired via an open application programming interface (API) to the COPD platform and presented in the clinical dashboard, to improve data visualisation for NIV clinical management alongside PROs and wearable data, and to inform and enhance other clinical encounters and patient–clinician communication.

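### No baseline-adjusted model is named for relating outcomes to NIV and self-management parameters, so baseline severity may confound these within-cohort associations

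*Protocol article*

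**What the plan says.** The Statistics and data analysis section names the methods: "Correlation, t-test, analysis of variance and effect size analyses will be used as appropriate for secondary endpoint analysis". The same sentence gives their use: "comparing results of clinical endpoint and patient-centred outcomes with NIV therapy and supported self-management parameters". No regression, ANCOVA or covariate is named for this purpose. The text does not call the analyses unadjusted, and it leaves the choice of method open.

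Other sections bear on the point:

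- **Baseline values of some outcomes are collected.** Table 1 lists "Hospital occupied bed days preceding and subsequent 12 months" and "Health-related quality of life (EQ-5D-5L) at baseline and monthly during study". The EHR data section takes hospital admissions and emergency attendances from 2010 onwards.
- **Severity is recorded at enrolment.** Baseline clinical data includes "participant age, sex, smoking status, vaccination status, comorbidities, COPD exacerbation history, COPD medications, lung function results".
- **NIV exposure depends on severity.** Under Remote-monitored home NIV, those started on it are "Participants with severe COPD who have standard indications".
- **Severity is controlled elsewhere.** Study design matches the SafeHaven control cohorts to RECEIVER on demographics, COPD severity and admission frequency.
- **Baseline factors have their own endpoint.** Table 1 separately lists the impact of previous admissions, lung function, smoking and other factors on outcomes. It does not say that they adjust the NIV and self-management comparisons.

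**The concern.** NIV parameters and self-management parameters (message threads, page views, rescue packs) are not assigned at random. Home NIV goes to people with severe disease, and people who start out sicker may also send more messages and use more rescue packs. The same people can be expected to have more admissions, more bed days and lower EQ-5D-5L scores. A simple correlation or comparison of group means then mixes two things: how ill the participant was at entry, and whatever relation exists between use and outcome.

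The mixing can work in either direction. It can produce an association where use has no effect, or hide a benefit because heavier users began in worse health. Matching to SafeHaven patients does not help, because these associations compare RECEIVER participants with one another. According to Study limitations, the experience gained will be the basis for later randomised studies, so a misleading association between use and outcome could carry into their design.

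**Working it through.** **No figure to reproduce.** The article states no power, significance level, effect size or correlation for these analyses. The 400 under Sample size is a feasibility figure. Everything below is an illustration on assumed correlations, with a two-sided 5% test.

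**Step 1: correlation produced by baseline severity alone.** Let a be the correlation of the parameter with baseline severity and b that of the outcome with baseline severity. If parameter and outcome are unrelated once severity is held fixed, their unadjusted correlation is r = a × b.

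**Step 2: how often that would be declared significant.** By Fisher's z, the shift is δ = atanh(r) × √(n − 3), and the rejection probability is Φ(δ − 1.96) + Φ(−δ − 1.96).

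| n | a | b | r = a × b | δ | Significant |
|---|---|---|---|---|---|
| 400 | 0.1 | 0.3 | 0.03 | 0.60 | 9% |
| 400 | 0.2 | 0.5 | 0.10 | 2.00 | 52% |
| 400 | 0.3 | 0.5 | 0.15 | 3.01 | 85% |
| 100 | 0.3 | 0.5 | 0.15 | 1.49 | 32% |

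The nominal rate is 5%. The last row matters because NIV usage and therapy parameters exist only for the NIV group. The article does not give the size of that group, so 100 is assumed.

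**Step 3: would change scores solve it?** Change from baseline does use the baseline value. Take severity to be the outcome's own baseline, with equal variance at both times. Under the same null, the correlation of the parameter with the change is (ab − a) / √(2(1 − b)). At a = 0.3 and b = 0.5 this is (0.15 − 0.30) / √1.0 = −0.15. The spurious association has the same size with the sign reversed.

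**Step 4: precision.** If the parameter were uncorrelated with baseline, adjustment at a baseline-outcome correlation of 0.5 would multiply the variance by 1 − 0.5² = 0.75. That cannot be combined with the stronger case of step 2, where the parameter correlates 0.3 with baseline. The factor is then 0.75 / (1 − 0.3²) = 0.75 / 0.91 = 0.82, a saving of about 18%. An analysis with 80% power would rise to Φ((1.96 + 0.84) / √0.82 − 1.96), about 87%. The 80% is only a reference value, since the plan sets no power target.

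**Limit of the arithmetic.** Bed days and admissions are counts, so linear correlations show the mechanism and do not forecast the error rate for those outcomes.

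**The case against.** The strongest reply is that the plan never says these analyses will be unadjusted. It lists families of methods to be chosen as fits. A paired t-test on bed days before and after entry, a repeated-measures analysis of EQ-5D-5L or a correlation of change scores would all use the baseline value. Covariate lists are also commonly left to the statistical analysis plan, which is not shown. This stands in part: a reader may not infer that the plan forbids adjustment. But a before-after test does not relate an outcome to a parameter at all, and a change score can carry a bias of its own (step 3). The point is directed at methods the article does name for this purpose, none of which is a baseline-adjusted model.

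Second, the study aims at feasibility, admits an inherent risk of bias and examines baseline factors in a separate endpoint. This lowers the stakes. It does not put adjustment into these comparisons.

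Third, baseline adjustment cannot reach all the bias. Rescue packs and self-management plans are activated because of exacerbations during follow-up, so the outcome partly causes the exposure. This stands and limits what the fix can claim.

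A reader might also go further and infer that baseline severity is what produces the associations, or that every outcome has a baseline counterpart. The article supports neither. It gives no correlations, so the size and even the direction are unknown. Bed days, admission or exacerbation history and EQ-5D-5L have baseline values; mortality does not.

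**Conclusion.** The concern holds as a risk of confounding. The named methods carry no stated baseline adjustment, the exposures are not randomised, NIV is given for severe disease, and the SafeHaven matching does not apply within the cohort. The data needed for adjustment are already collected.

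The size depends wholly on assumed correlations. From weak (0.1 and 0.3) to stronger (0.3 and 0.5) confounding, a null association would be called significant about 9% to 85% of the time with all 400 participants, and about 32% in the stronger case with 100 NIV users. Any gain in precision is secondary and breaks no claim in the plan.

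A reader might infer that the trial's main result or its external-control comparison is affected. The documents do not support that. The primary endpoint is a utilisation proportion that these tests do not touch, and the SafeHaven cohorts are already matched on severity and admission frequency.

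**What to change.** In Statistics and data analysis, state that associations of outcomes with NIV and self-management parameters will be estimated by regression that includes the participant's own baseline value of the outcome where one exists:

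- **Bed days, admissions and exacerbations:** a count model such as negative binomial, with the preceding-12-month value as covariate and log follow-up time as offset.
- **EQ-5D-5L:** ANCOVA or a mixed model for the monthly values, with baseline EQ-5D-5L as covariate.
- **All models:** age, sex, smoking status, lung function and entry cohort (home NIV or exacerbation), the last where the analysis includes both cohorts.

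Report the unadjusted correlations, t-tests and ANOVA as descriptive only. Add a sentence that adjustment reduces confounding without removing it, in particular for rescue-pack use and other parameters triggered by exacerbations during follow-up.

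The cost is wording and a little more analysis on data already held, with no new visits or participants. The downsides are small: missing baseline EQ-5D-5L needs a stated rule, and adjusted estimates are slightly less simple to present.

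### Self-management use is counted over the same 12 months as the outcomes it is tested against, with no allowance for time at risk, so use looks protective against death and can look harmful for event counts

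*Protocol article*

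**What the plan says.** Under Statistics and data analysis the article names the tests, "Correlation, t-test, analysis of variance and effect size analyses will be used as appropriate for secondary endpoint analysis", and the comparison they serve, "comparing results of clinical endpoint and patient-centred outcomes with NIV therapy and supported self-management parameters". The clinical endpoints themselves are summarised separately: "The clinical endpoint data will be reported as a proportion and 95% CI for that outcome, calculated by Kaplan-Meier method".

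Table 1 (Study outcome measures) gives the self-management parameters. They include "utilisation of self-management information (page views"), "utilisation of messaging (number of message threads") and "number of rescue packs used in 12 months (captured through weekly PROs"). The third is explicitly a 12-month total. The first two are counts with no stated denominator. The NIV entry lists usage and therapy parameters without saying whether usage is a total or a nightly average.

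The outcome window is in Subsequent assessments: "Observation of secondary endpoints will be continued over the 12-month period following recruitment". Table 1 lists mortality, exacerbation, unscheduled contacts and hospital admission among the clinical events. It corrects for survival shorter than 12 months only for occupied bed days. Withdrawal of subjects keeps withdrawn participants in the analyses and lets the investigator withdraw someone nearing the end of life.

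**The concern.** A count gathered after enrolment depends on how long the person was there to be counted. When it is then tested against an outcome from the same period, exposure and outcome are linked by construction, and the named tests use neither time at risk nor time order.

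The link can run in two directions:

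- **Death.** Early death cuts use short, so low use goes with death and use looks protective.
- **Event counts not scaled by time alive.** Early death cuts both use and events short, so the two correlate positively and use looks harmful. Exacerbations also prompt messages and rescue-pack use, which pushes the same way. A rescue-pack count is close to being an exacerbation count itself.

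The trial could therefore report that engagement improves survival, or that messaging goes with more exacerbations, when neither reflects an effect of the service. The article says (Study limitations) that this experience will inform later randomised studies, so a spurious engagement result could be carried forward.

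**Working it through.** The article gives no figure for this comparison, so there is none to reproduce. The check asks what the stated metrics and tests return when use has no effect.

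**From the article:** planned N = 400 (Sample size); 12-month window; use recorded as counts. **Assumed, because not given:** 12-month mortality p of 10%, 20% or 30%; constant hazard; use rate independent of death unless stated.

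**Step 1: time available to those who die.** With hazard λ = −ln(1 − p), mean time alive among those dying within the year is 1/λ − (1 − p)/p.

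- p = 10%: λ = 0.1054; 9.491 − 9.000 = 0.49 years
- p = 20%: λ = 0.2231; 4.481 − 4.000 = 0.48 years
- p = 30%: λ = 0.3567; 2.804 − 2.333 = 0.47 years

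People who die thus accumulate just under half the use of survivors with the same underlying rate. At an assumed 12 messages a year and p = 20%, that is 12 × 0.48 = 5.8 against 12.

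**Step 2: mortality by message count.** Simulation, 2,000 runs, N = 400, individual message rates gamma with shape 1 and mean 12 a year.

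| 12-month mortality | Above median | At or below median | Gap (points) |
|---|---|---|---|
| 10% | 5.2% | 14.5% | 9.3 |
| 20% | 10.9% | 28.2% | 17.3 |
| 30% | 17.6% | 41.5% | 23.9 |

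**Step 3: the named tests.** A separate simulation (2,000 runs; mean use 20 a year, coefficient of variation 0.8; withdrawal 0% or 10%; admissions mean 1.5 a year, overdispersed and unrelated to use) gave these shares of null runs with p < 0.05:

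- t-test of cumulative use, dead versus alive, N = 400: 97–98% at 10% mortality and 100% at 20–30%, with mean t from −3.6 to −6.4. At N = 100: 42–48%, 76–81% and 89–92% at 10%, 20% and 30% mortality.
- Correlation of cumulative use with raw admission count, N = 400: mean r about +0.03 to +0.09, p < 0.05 in 10–42%. The sign is the opposite one.
- Correlation with admissions per time alive: about 5%.
- Mean nightly NIV hours, dead versus alive: about 5%, so a nightly average carries no bias from follow-up length.

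**Step 4: the remedies, same null.** Use per unit of follow-up: 6–9% at N = 400, mean t about 0. Three-month landmark: about 5–6%. In the step 2 model at 20% mortality, the landmark comparison is 15.3% against 15.4%.

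**Step 5: severity drives both.** Let one frailty (gamma, mean 1, variance 0.25) multiply both the message rate and a death hazard of 0.25 a year. The cumulative gap falls from 18.8 points (12.3% v 31.1%) to 12.6 (15.0% v 27.6%). An unadjusted landmark now gives 19.2% above the median against 14.7% below. That residual is confounding by severity, and it is why the remedy needs baseline adjustment as well.

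**The case against.** **The article does not spell out the faulted analysis.** It does not say which outcome is paired with which parameter, the tests apply as appropriate, and scaling by time is the kind of detail a statistical analysis plan would settle. The missing pairing stands as a limit. The rest does not remove the point: the article itself fixes both the test family and the count metrics, none of the named tests uses time order, and it corrects for short survival for bed days but not for these counts. Kaplan-Meier handles censoring of the outcome, not an exposure accumulated after baseline.

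**These are unpowered secondary analyses in a feasibility study that admits bias.** True, and it limits the severity. But Study limitations speaks of bias in general and does not name this one, and the tests are still planned.

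**Stronger readings that the documents do not support:**

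- A reader might infer that NIV use is affected in the same way. Table 1 does not say NIV usage is cumulative, and a nightly average would not carry this artefact, although falling use before death could still bias it.
- A reader might infer that use will look protective throughout. That holds for death; for unscaled event counts the sign can reverse.
- A reader might infer that withdrawal acts like death. It gives a protective look only if it is tied to the outcome and outcomes are still captured afterwards. End-of-life withdrawal makes this plausible, but it is not established.
- A reader might infer that this analysis decides which service components go forward. The article assigns the prioritising of data inputs to the machine learning work (Study design) and service changes to adoption experience (Service model iterations).

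**Conclusion.** The point holds for supported self-management counts. Tested as described, they give a biased association: protective for death, and possibly harmful for event counts not scaled by time alive or for use prompted by exacerbations.

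The size rests on assumptions. With 10% to 30% mortality and no true effect, the spurious mortality gap is roughly 9 to 24 points and is smaller if severity drives both use and death. No single value should be quoted as the trial's expected bias. The primary endpoint is unaffected. This should be corrected, but it does not threaten the trial's main result.

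**What to change.** In Statistics and data analysis, or in the analysis plan, state that:

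1. Self-management use and event outcomes are expressed per unit of time at risk.
2. Use is measured before the outcome. One option is a landmark: weekly use rate in months 0 to 3 against events in months 3 to 12, among participants alive and under follow-up at 3 months, adjusted for prior-year admissions and, where available, other baseline severity measures. The other is a time-updated model with use lagged before each event.
3. Rescue packs are not used as an explanatory variable for exacerbations.
4. Results are reported as associations, not effects of use.
5. NIV usage is defined as a nightly average or a total; if a total, items 1 and 2 apply to it too.

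The platform tracking and episode feeds under Secondary endpoint measures should supply the dates, so the change is to analysis wording. The cost of the landmark version is that events in the first 3 months are not used; the time-updated model avoids this but is more complex. Scaling by time at risk alone removes the follow-up-length artefact but neither reverse causation nor confounding by severity.
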